### Outcome and statistical analyses

For all planned analyses baseline data will be presented with descriptive statistics; continuous variables as mean with standard deviation and categorical variables as frequency with percentages. A detailed overview of research questions and statistical analyses are described in the following section. All analyses will be performed using SPSS v 23 (IBM Corp. Armonk, NY) and STATA v 16 (Stata Corporation LP; College Station, TX, USA).

**Research question 1:** Which are the clinical predictors and biomarkers predictors of pain response to palliative RT for CIBP?

*Objective*: To obtain demographic, clinical data and biomarkers before start of RT and compare with RT response for pain in order to develop a classification system relevant for predicting RT response.

*Outcome*: Primary endpoint is response to RT defined as at pain reduction of worst pain score of two or more at the treated site on the 11-point NRS together with no increase in analgesic intake, or a reduction in opioid intake of at least 25% from baseline without an increase in worst pain score at the treated site [18]. Patients with two or more radiation locations are defined as responders if they respond in one of the included sites. Patients who die before the first assessment (3 weeks after RT), will be defined as non-responders because these patients have not benefited from RT. Patients with missing data on outcome measurements including pain intensity at the treated site or the use of analgesic medications will not be included in the analyses.

*Statistical method*: Clinical variables (see previous chapter) and CRP will be included in a multivariate logistic regression model to predict potential factors for response to RT. The model will be adjusted by study centre. Regression diagnostics will be performed for all analyses adding interactions terms if necessary. Significant variables from the multivariable model will be presented as a response-score to determine the likelihood of response to RT. Second, we will perform analyses on inflammatory biomarkers and bone biomarkers correlated with response to RT. Only inflammatory biomarkers and bone biomarkers with levels of serum concentrations above the detection threshold and which have a variability between measurements will be analysed with a multivariate logistic regression model with response to RT as the dependant variable. Finally, an integrated regression model with response to RT including both the significant clinical variables and significant biological biomarkers will be conducted if appropriate based on results from the previous analyses.

**Research question 2:** Which inflammatory biomarkers are associated with change in pain intensity in patients with CIBP?

*Objective*: To investigate the correlation between pain intensity and inflammation. Patients included in the PRAIS study all have CIBP and will receive a standardized intervention expected to give pain relief in about 60% of the patients. This study can explore if there is a longitudinal relationship between changes in pain intensity and the detected level of inflammatory biomarkers.

*Outcome*: Serum concentrations of inflammatory biomarkers as described above associated with changes in pain intensity as measured by average pain intensity and worst pain intensity last 24 h (NRS 0–11) for a maximum of 1 year follow-up.

*Statistical method*: Longitudinal data analysis with repeated measurements using a liner mixed effect model or generalized estimating equation (GEE).

**Research question 3:** Which inflammatory substances are associated with cancer cachexia?

*Objective*: To gain insight into the role of inflammation in cancer cachexia.

*Outcome*: Cachexia is defined as a) weight loss > 5% over past 6 months (in absence of simple starvation); or b) body mass index (BMI) < 20 and any degree of weight loss > 2%; or c) appendicular skeletal muscle index consistent with sarcopenia (males < 7・26 kg/m2; females < 5・45 kg/m2) and any degree of weight loss > 2% [38]. Cachexia severity is assessed as degree of weight loss and EORTC QLQ C15 PAL physical function and appetite loss.

*Statistical method*: Fist, we will perform a cross-sectional analysis in the baseline parameters using a logistic regression with cachexia as outcome, and the various inflammatory markers as explanatory variables. Second, we will investigate the association between changes in inflammatory markers over time and cachexia severity using mixed linear modelling.

**Research question 4:** Which inflammatory substances are associated with depression in cancer patients?

*Objective*: To explore the associations between serum concentrations of inflammatory substances and depression.

*Outcome*: Depression is measured by the PHQ-9 questionnaire [57]. The PHQ-9 includes 9 items identical to the diagnostic criteria (i.e. the depression symptoms) for depression disorder. For the purpose of these analyses we will use depressive disorder as defined by the PHQ-9 recommended sum score calculation, and symptom by symptom in the PHQ-9 score in associations of serum concentrations of inflammatory biomarkers during a period of 1 year form inclusion.

*Statistical method*: We will use repeated measurements and a linear mixed effect model to perform the analyses.

**Research question 5:** Which are the clinical predictors and biomarker predictors of development of cachexia in patients with metastatic cancer disease?

*Objective*: To obtain demographic and clinical data and biomarkers in a homogenous population of patients with metastatic cancer, and within a prospective, longitudinal follow-up study observe which factors predicting the development of severe cachexia during one-year follow-up.

*Outcome*: Cachexia is defined as for research question 3.

*Statistical method*: As the purpose is to evaluate development of cachexia, only patients without cachexia at baseline will be included in this analysis. A Cox regression will be used to evaluate baseline predictors of cachexia development.

**Research question 6**: What is the relationship between pain reduction and depression in patients receiving RT for CIBP?

*Objective*: RT is expected to reduce pain in a substantial number of patients. This creates a possibility to study the relationship between depression and pain longitudinally in an experimental-like design in which one variable (pain) is manipulated and the effect on another related variable (depression) is studied.

*Outcome*: Depression is measured as for Research question 4.

*Statistical method*: Longitudinal analyses with repeated measurements analyzed with a linear mixed effect model.

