#### Inclusion criteria

Verified cancer diagnosis, including hematological malignancies (based on radiological, histological, cytological or operative evidence)Bone metastases verified either by x-ray, bone scan, computer tomography (CT) or magnetic resonance imaging (MRI)Patients that are about to undergo RT with palliative intent for painful bone metastasesRT to be administered within 1 week after baseline observations are obtainedAge ≥ 18 yearsPatient able to comply with trial procedures

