#### Clinical variables

At inclusion the following information will be collected (variables included as independent variables in the primary analyses are denoted with an asterisk): Age^*^, gender^*^, ethnicity, height, comorbidity^*^ (Charlson Comorbidity Index) [51], Karnofsky performance status^*^ [52], living situation, educational level, alcohol use, smoking status^*^, type of department (palliative care unit, surgical ward, general oncology ward, out-patient clinic, other), oncological history related to the current cancer disease (tumor diagnosis^*^, time since cancer diagnosis^*^, presence of metastases other than bone^*^, osteolytic metastasis at each planned site for RT^*^, soft tissue expansion at each planned radiation site^*^, previous and on-going anti-cancer treatment: (RT, surgery, chemotherapy, hormonal treatment, other interventions – for the primary analyses current oncological treatment other than RT (Y/N)^*^), planned RT (fractions^*^, total dose^*^ and anatomical region; narrow to radiation location in weight bearing bone (Y/N) for the primary analyses^*^, re-irradiation, previous pain treatments (duration of opioid treatment and previous unsuccessful trials with other opioids) and medications and doses for the previous 24 h (for the primary analyses we will include opioid dose in oral morphine equivalents last 24 h^*^and steroids^*^). In addition, an objective measurement of lean body mass, measured by CT scan of L3 and/or Th4 vertebrae will be performed at baseline.

At both baseline and at all follow-up visits the following self-reports will be collected: Health related quality of life (EORTC QLQ-C15 PAL) [53] (for the primary analyses trouble sleeping^*^, nausea^*^ and constipation^*^ will be included as variables), nutritional status (PG-SGA) [54], weight, overall and site specific average and worst pain last 24 h (BPI) [55] (for the primary analyses “worst pain last 24h”^*^), pain at rest and at movement from each planned irradiated site [56] (for the primary analyses we will use the variable that reflects worst pain at the irradiated site at baseline^*^) and depression^*^ (PHQ9) [57]. Specific questions related to episodic pain^*^ and self-report neuropathic symptoms and signs^*^ (LANSS) [58] will be asked at baseline and after 3 and 8 weeks.

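### Baseline pain at the treated site is a candidate predictor of an endpoint computed from it, so it will probably earn response-score points even if RT works equally at every pain level

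*Protocol article*

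**What the plan says.** Under research question 1 (Outcome and statistical analyses), a patient responds by either of two routes:

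- Pain route: a "pain reduction of worst pain score of two or more at the treated site on the 11-point NRS", with no increase in analgesics.
- Opioid route: "a reduction in opioid intake of at least 25% from baseline without an increase in worst pain score at the treated site".

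A patient with several irradiated sites is a responder if any one of them responds.

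The Inclusion criteria ask that patients be "about to undergo RT with palliative intent for painful bone" metastases. Neither these nor the Exclusion criteria give a minimum NRS score.

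Clinical variables marks the candidates for the primary model. On site pain: "for the primary analyses we will use the variable that reflects worst pain at the irradiated site at baseline". On opioids: "for the primary analyses we will include opioid dose in oral morphine equivalents last 24 h". Overall worst pain over 24 hours is marked as well.

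The statistical method for research question 1 enters the clinical variables and CRP in one logistic model and then states: "Significant variables from the multivariable model will be presented as a response-score to determine the likelihood of response to RT". The article does not mention patients who cannot meet a route, or the link between baseline pain and a change-based endpoint.

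**The concern.** Two consequences follow from the definition.

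First, some patients are non-responders whatever RT does. With worst pain 0 or 1 at every treated site, the score cannot fall by 2. With no opioid dose, there is nothing to cut by 25%. A patient in both positions is recorded as a failure.

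Second, and more important, baseline site pain enters both sides of the model. A high score has room to fall and tends to fall on remeasurement. A low score has little room and tends to rise. Baseline pain can thus be strongly associated with response although RT does the same for everyone.

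This matters because of the intended use. The Background seeks patients likely to respond poorly, who should then not receive RT, and the Discussion speaks of sparing patients futile treatment. The cohort has no untreated comparator, so a baseline-pain term in the score is easily read as less RT benefit in mild pain. The Background also reports high baseline pain as a predictor in one of two earlier papers, so a finding here would look like confirmation. The validation sample that was dropped would not have exposed the problem, because it would have used the same endpoint.

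**Working it through.** The article states no pain distribution, response variance or opioid prevalence, and no figure on this point to reproduce. Step 1 is exact; the rest rests on stated assumptions.

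**1. What the definition fixes.** Pain route: follow-up score ≤ baseline − 2. At baseline 0 or 1 this needs a negative score, so it is impossible. Opioid route: follow-up dose ≤ 0.75 × baseline dose. At dose 0 no reduction exists. With both, the probability of response is 0.

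**2. Size of the fixed non-responder group.** Assume worst site pain has mean 6 and SD 2.5, rounded to whole points, and that 60% use opioids independently of pain.

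- P(score 0–1) = Φ((1.5 − 6)/2.5) = Φ(−1.8) = 0.036.
- Without opioids as well: 0.036 × 0.40 = 0.014, or about 9 of 600.

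This treats each patient as having one site; with several sites the share is smaller.

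**3. Regression to the mean, pain route only, no RT effect.** With retest correlation r, follow-up given baseline b has mean 6 + r(b − 6) and SD 2.5√(1 − r²). With rounding, a 2-point drop means follow-up below b − 1.5.

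| r | baseline | mean | SD | z | P(drop ≥ 2) |
|---|---|---|---|---|---|
| 0.7 | 4 | 4.6 | 1.785 | (2.5 − 4.6)/1.785 = −1.18 | 12% |
| 0.7 | 8 | 7.4 | 1.785 | (6.5 − 7.4)/1.785 = −0.50 | 31% |
| 0.5 | 4 | 5.0 | 2.165 | (2.5 − 5.0)/2.165 = −1.15 | 12% |
| 0.5 | 8 | 7.0 | 2.165 | (6.5 − 7.0)/2.165 = −0.23 | 41% |

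For r = 0.7 the odds are 0.443 at baseline 8 and 0.136 at 4. Over four points, (0.443/0.136)^(1/4) = 1.34 per point. Simulated logistic slopes over the whole scale give odds ratios of 1.33 (r = 0.7) and 1.47 (r = 0.5).

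**4. The same with an RT effect unrelated to baseline.** Take a mean effect of 2 points, SD 2. For r = 0.7 the follow-up SD is √(1.785² + 2²) = 2.68.

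- Baseline 8: Φ((6.5 − 5.4)/2.68) = 66%.
- Baseline 4: Φ((2.5 − 2.6)/2.68) = 49%.

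Simulated odds ratios per point are 1.24 and 1.36 (r = 0.7 and 0.5), with about 55% responding. With a mean effect of 2.5 points they are 1.26 and 1.38, with about 61–62% responding, close to the 60% the article expects.

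**5. Full two-route endpoint.** A second simulation used stable pain SD 2 and error SD 1.5 (total SD √(4 + 2.25) = 2.5, retest correlation 4/6.25 = 0.64). It assumed 60% opioid users, of whom 20% cut their dose by at least 25%, and an analgesic increase in 25% of users and 15% of non-users.

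| Mean RT effect | response at baseline 0–1 | at 6 | at 10 | OR per point | AUC | OR, opioid use |
|---|---|---|---|---|---|---|
| 0 | 3% | 22% | 40% | 1.31 | 0.67 | 1.36 |
| 2 | 7% | 48% | 59% | 1.20 | 0.61 | 0.99 |
| 2.5 | 8% | 53% | 63% | 1.19 | 0.61 | 0.94 |

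AUC is for baseline pain and opioid use together. At N = 600 × 0.8 = 480, baseline pain was significant at 5% in 99.7–100% of 300 runs per scenario. These models held only those two predictors. In the planned model, overall worst pain is correlated with site pain and may share the signal.

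**6. Would a minimum score remove it?** Requiring baseline ≥ 2 moves the odds ratio in the step 5 model from 1.31 to 1.29 with no effect, and from 1.20 to 1.16 with a 2-point effect. Most of the link remains.

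**The case against.** Much of the opposing case is sound. The endpoint follows a cited consensus. A baseline score is a legitimate covariate for a change-based outcome, and adjusting for it protects the other predictors. A score meant to give the likelihood of response loses calibration if known terms are left out. Separating RT effect from natural course is impossible for any predictor in a single cohort. All of this stands, and it is why baseline pain should stay in the model. It does not answer the point about interpretation: for baseline pain the association is expected from the definition alone, and the article plans to score it without saying so.

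A reader might infer four stronger things that the document does not support.

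- **That opioid dose also predicts by construction.** Non-users lose one route, but users may more often fail the no-increase condition, and among users a 25% relative cut does not depend mechanically on dose. The simulated odds ratio for opioid use ran from 1.36 to 0.94, so the definition fixes neither sign nor size.
- **That overall worst pain is part of the endpoint.** It is not; the endpoint uses worst pain at the treated site. The marked site variable follows a mention of pain at rest and on movement, so it may not be exactly the endpoint's baseline score, though it is described as worst pain at the irradiated site.
- **That the missing entry threshold is the main defect.** Painful metastases are required, the affected group is small, and a threshold of 2 hardly changes the link. It would also remove opioid users who can still respond by the opioid route.
- **That baseline pain takes accuracy away from real predictors.** With joint entry of the variables this is not shown.

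A supporting model could be left to an analysis plan that is not shown. The endpoint, the predictor list and the scoring rule are, however, fixed in the article.

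**Conclusion.** The point holds in a limited form. Without any assumption, a patient with worst pain 0–1 at every treated site and no opioid use cannot be a responder but counts as a failure. That is a small group, about 1–2% under the assumed distributions. Under the same kind of assumptions (mean NRS 6, SD 2.5, retest correlation 0.5 to 0.7), baseline site pain carries an odds ratio of about 1.2 to 1.5 per point, with no RT effect or with one unrelated to baseline. It will therefore very probably reach significance and earn score points. The direction follows from the endpoint; the size depends on distributions that the article does not give. No such conclusion is available for opioid dose. The point merits a change because the score is meant to inform who is spared RT.

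**What to change.** Change the analysis wording for research question 1:

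1. Leave out of the responder model, and describe separately, patients who at baseline can meet neither route: worst pain 0–1 at every treated site and no opioid dose. Keep opioid users with low pain scores, since the opioid route is open to them.
2. Keep baseline site pain and opioid dose as covariates. Report the score's discrimination beyond a model holding these baseline values alone. State that the baseline-pain coefficient, and any points it earns, do not show lower RT benefit in patients with mild pain.
3. Add a supporting model of follow-up worst pain at the treated site, adjusted for baseline, to confirm the other predictors. It cannot vindicate baseline pain itself, because a baseline score naturally predicts the follow-up score.

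No new data are needed, and recruitment is already closed. The cost is that a few patients leave the primary set (about 9 of 600 under the assumptions above) and that the score's reported added accuracy may be less favourable.

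### The any-site responder rule makes response more likely with more irradiated sites, but the primary model does not adjust for number of sites

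*Protocol article*

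**What the plan says.** Under Outcome and statistical analyses, research question 1, response is defined at the treated site in two ways. One is "pain reduction of worst pain score of two or more at the treated site on the 11-point NRS together with no increase in analgesic intake". The other is "a reduction in opioid intake of at least 25% from baseline without an increase in worst pain score at the treated site". For patients treated at several sites the article adds: "Patients with two or more radiation locations are defined as responders if they respond in one of the included sites". It gives a reason for counting deaths before week 3 as non-responses, but none for this rule.

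The statistical method is one patient-level logistic regression on the marked clinical variables and CRP, adjusted for study centre. Its significant variables become a response score.

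The marked variables are listed under Clinical variables. Several belong to a site rather than a patient: "osteolytic metastasis at each planned site for RT", "soft tissue expansion at each planned radiation site", and the anatomical region, which is reduced as follows: "narrow to radiation location in weight bearing bone (Y/N) for the primary analyses". For site pain the article says "we will use the variable that reflects worst pain at the irradiated site at baseline", in the singular. Number of irradiated sites is not marked. The article names no index site and does not say how several sites are reduced to one value.

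**The concern.** A patient with two treated sites has two opportunities to be a responder, and a patient with three has three. The scoring rule therefore builds an association between number of sites and response before any biology enters. With number of sites outside the model, part of that association passes to whatever accompanies multi-site treatment. Tumour diagnosis, metastases outside bone, performance status and opioid dose are all in the model and could plausibly differ by number of sites. A variable could then enter the response score because of how response was counted.

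A second issue is confined to multi-site patients. The outcome asks whether any site responded, while osteolysis, soft tissue expansion, weight-bearing location and site pain describe particular sites. The site that responds need not be the one whose features enter the model. Lesion appearance and soft tissue expansion matter here because the Background names them as gaps in earlier prediction work. Under Power consideration the planned validation sample is dropped, so no held-out data from this study will test the score.

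**Working it through.** **Inputs from the article.** The any-site rule; the predictor list without number of sites; adjustment for centre; and an expected response described as a "standardized intervention expected to give pain relief in about 60% of the patients".

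**Assumptions.** The 60% is a per-patient figure and is used here as a per-site rate p. Within-patient correlation (rho, on a latent normal scale) and the share of multi-site patients are not given, so ranges are shown.

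**The plan's own arithmetic.** 10 × 29 variables = 290, as stated under Power consideration. It does not depend on the any-site rule and is not in question.

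**Step 1: effect of number of sites from the rule alone.** Under independence, P(any of k sites responds) = 1 − (1 − p)^k. For p = 0.6 this is 1 − 0.4² = 0.84 for two sites and 1 − 0.4³ = 0.936 for three. For correlated sites an exchangeable latent-normal model was integrated numerically. The odds for a single site are 0.6/0.4 = 1.5.

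| rho | one site | two sites | three sites | OR, two v one |
|---|---|---|---|---|
| 0 | 60% | 84% | 94% | 3.5 |
| 0.3 | 60% | 79% | 88% | 2.6 |
| 0.5 | 60% | 76% | 83% | 2.1 |
| 0.8 | 60% | 70% | 75% | 1.5 |
| 1 | 60% | 60% | 60% | 1.0 |

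Example at rho = 0.5: (0.761/0.239)/1.5 = 2.1. With an assumed per-site rate of 40%, the two-site odds ratios are 2.7 (rho 0), 1.9 (0.5) and 1.5 (0.8).

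**Step 2: leakage into a predictor with no effect.** Let q be the two-site probability and s the share of two-site patients in a predictor group. The group's response rate is 0.6(1 − s) + q·s. These odds ratios are unadjusted; other covariates in the model could absorb part of them.

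| two-site share with v without the predictor (assumed) | rho 0 | rho 0.5 | rho 0.8 |
|---|---|---|---|
| 50% v 20% | 1.40 | 1.24 | 1.14 |
| 20% v 10% | 1.11 | 1.07 | 1.04 |

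Example, first row at rho = 0: 0.5 × 0.6 + 0.5 × 0.84 = 0.72 against 0.8 × 0.6 + 0.2 × 0.84 = 0.648. The odds ratio is (0.72/0.28)/(0.648/0.352) = 1.40.

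**Step 3: site-level predictors.** A large simulation used a site feature of 50% prevalence with a true site-level odds ratio of 2.0, at rho 0 and 0.5.

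| two-site patients (assumed) | one site's value used | coded as present at any site |
|---|---|---|
| 0% | 2.0 | 2.0 |
| 40% | 1.8 | 2.2 to 2.5 |
| 100% | 1.5 to 1.6 | 1.7 to 1.9 |

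A feature with no effect, coded as present at any site, with 50% prevalence and 30% two-site patients, shows about 1.26 (rho 0) or 1.16 (rho 0.5). The direction of the bias therefore depends on the coding.

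**The case against.** The strongest defence is that the rule is explicit, set in advance, and answers a coherent patient-level question: did this patient gain relief at any treated site? The study aims to identify patients likely to benefit, so this is a legitimate outcome. That stands, and it is a reason to keep the endpoint.

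Size is the next point. A reader might infer from the independence figures that an odds ratio of 3.5 swamps any real predictor. The article does not support that. Any increase in analgesic intake bars every site from the pain criterion, the opioid reduction is shared by all sites, and death before week 3 makes the whole patient a non-responder. Sites are therefore positively correlated, and 3.5 is a bound that cannot be reached. The two-site odds ratio also describes number of sites, which is not a reported predictor. What reaches the modelled variables is the much smaller leakage in Step 2, which is slight if few patients have several sites.

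A reader might also infer that site-level effects are necessarily diluted, or that outcome and predictors are disconnected throughout. Neither holds. Coding a feature as present at any site can inflate its effect, and in single-site patients outcome and predictors match. How site values are collapsed may be settled in a fuller document that is not shown, so its absence from the article is not itself a fault.

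The defence does not remove the central point. The article fixes both the any-site rule and the predictor list, and nothing in that list absorbs the number of sites.

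**Conclusion.** The point holds in limited form. As written, the primary model lets number of irradiated sites influence response through the definition alone, without adjustment. The direction is certain unless sites within a patient respond identically. The size is not. It is an odds ratio of about 1.5 to 2.1 for two sites versus one at correlations of 0.8 to 0.5, and roughly 1.04 to 1.40 for a null predictor associated with multi-site treatment, where the top value assumes independence. These figures rest on a per-patient 60% used per site and on assumed correlations and multi-site shares. Site-level predictors in multi-site patients may be biased up or down.

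A reader might conclude that the primary endpoint must be replaced by response at a single index site. The documents do not require that. Recruitment has closed, the any-site question is coherent, and an index site chosen for the highest baseline pain would invite regression to the mean and discard response at the other sites.

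**What to change.** Keep the any-site endpoint if the patient-level question is the one wanted, and make these changes before the outcome is analysed:

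1. Add number of irradiated sites as a covariate in the primary logistic model, whether or not it is significant.
2. Repeat the primary model in single-site patients, where outcome and site features refer to the same lesion.
3. Fit a site-level logistic model, by GEE or with a random patient intercept, pairing each site's response with that site's own features.
4. State how each site-level predictor is reduced to one value in the patient-level model, and report the distribution of number of sites so that readers can judge the size of the problem.

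No new data are needed, since site-specific pain is already collected at baseline and at follow-up. The cost is one more model term and a little more analysis work. The single-site analysis will be less precise because it uses fewer patients.

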Imaging techniques may also be helpful to predict RT response. Two studies have demonstrated that low uptake on FDG PET-CT before RT predicted better RT response [21, 22]. MRI have also been proposed to predict RT response, but the published results are so far inconsistent [23, 24]. In addition both PET and MRI is time and economically difficult to establish as routine care. Biomarkers such as urinary osteoclast markers have been proposed to predict RT response in patients with bone metastases [25, 26], but this association is not present in all trials [27]. Elevated C-reactive protein (CRP) levels are related to more advanced disease in cancer patients that undergo palliative RT, but as far as we know no studies demonstrate a relationship between the level of CRP or other inflammatory markers and RT response in patients with CIBP [28]. Previous published literature on clinical predictors for response to RT has also no information about radiographic appearance of metastases like sclerotic/osteolytic metastases, soft tissue expansion outside bone, other cancer related symptoms or biomarkers as potential predictors.

Thus, there is still not enough information to predict which patients who are likely to respond poorly, and consequently should not receive RT. To identify patients who have increased likelihood of successful analgesia from palliative RT would improve cancer pain management.

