### Expected limitations

As for all studies on palliative cancer patients we expect the number of drop-outs and missing data to be relatively high. A reason for drop-out before evaluation of treatment response may be that the patients are too sick or because of high symptom burden. These patients cannot be included in the predictive analyses as they are not missing at random and may bias the results. The patient inclusion is also for practical reasons not consecutive and the sample size of 600 do not allow for a validation sample analyses. Also, in order to assess the adverse effects from RT, a day-to-day evaluation of symptoms after RT would have given important information but were not performed in order to simplify data collection for the patient population.

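### Research question 1 counts deaths before week 3 as pain non-response in the biomarker models too, so a marker of early death can look like a predictor of pain response

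*Protocol article*

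**What the plan says.** All of the following is in the protocol article. Under Outcome and statistical analyses, Research question 1 asks: "Which are the clinical predictors and biomarkers predictors of pain response to palliative RT for CIBP". The endpoint combines a fall in worst pain at the treated site with analgesic use. Two groups have no pain score after RT, and each has its own rule:

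- Early deaths: "Patients who die before the first assessment (3 weeks after RT), will be defined as non-responders because these patients have not benefited from RT".
- Missing outcome data: "Patients with missing data on outcome measurements including pain intensity at the treated site or the use of analgesic medications will not be included". Expected limitations says of patients who drop out before evaluation, for instance because they are too sick: "These patients cannot be included in the predictive analyses as they are not missing at random and may bias the results".

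The resulting binary outcome then serves three models. The clinical variables "and CRP will be included in a multivariate logistic regression model to predict potential factors for response to RT". Next: "Second, we will perform analyses on inflammatory biomarkers and bone biomarkers correlated with response to RT"; markers that are detectable and vary "will be analysed with a multivariate logistic regression model with response to RT as the dependant variable". No clinical covariates are named at this second step. Finally, an integrated model combines the significant clinical variables and significant markers, if appropriate.

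On what CRP reflects, the Background section on prediction of RT response says: "Elevated C-reactive protein (CRP) levels are related to more advanced disease in cancer patients that undergo palliative RT".

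**The concern.** For a patient who died before week 3, nobody knows whether the pain at the treated site responded. The label non-responder is correct if the outcome is being alive with pain relief. It is not an observation about pain. A binary logistic model cannot separate pain that did not respond from death before assessment, so any marker that is higher in patients close to death acquires a negative association with response, even if it is unrelated to analgesia among survivors.

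The article itself links CRP to advanced disease. Its section on cancer-related symptoms and inflammation adds that it is hard to tell whether inflammation only tracks disease severity or itself produces symptoms. Coding early death as pain non-response brings that ambiguity into the outcome. What is at stake is the label on a positive result: predictor of pain response to RT, or predictor of death within weeks.

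The two unassessed groups are also handled in opposite ways. Early deaths stay in as failures. Living patients too sick to be assessed are left out because they are not missing at random, although that reason describes early deaths equally well.

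**Working it through.** **The plan's own figure.** Power consideration gives 10 × 29 variables = 290, which reproduces. Allowing for 20% loss gives 290 / 0.8 = 363. The further step to 600 rests on an unquantified allowance for interactions; it cannot be reproduced and is not at issue here.

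**Inputs.**

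- From the article: 600 patients recruited, up to 20% lost to follow-up, pain relief expected in about 60%.
- Evaluable n: 600 × 0.8 = 480, taken to include early deaths (assumption).
- Response among survivors: 60%, whatever the marker value (the null case for pain).
- Test: two-sided 5% (assumption; the article states no alpha).
- Early-death rate d: not given; 2-15% assumed.
- Marker-death association: not given; odds ratio (OR) for death 1.5, 2 or 3 per SD assumed.

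**Share of non-responders who are early deaths:** d / (d + 0.4(1 − d)).

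- d = 2%: 0.02 / 0.412 = 5%
- d = 5%: 0.05 / 0.430 = 12%
- d = 10%: 0.10 / 0.460 = 22%

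**Simulation** (3,000 runs per setting, logistic regression on a continuous marker that acts only on death). Chance that the marker is significant for response:

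| Early deaths (of 480) | OR 1.5 | OR 2 | OR 3 |
|---|---|---|---|
| 2% (10) | 0.06 | 0.07 | 0.08 |
| 5% (24) | 0.08 | 0.15 | 0.26 |
| 10% (48) | 0.16 | 0.35 | 0.65 |
| 15% (72) | 0.27 | 0.59 | 0.89 |

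The mean spurious OR for response per SD runs from 0.98 (2%, OR 1.5) to 0.74 (15%, OR 3). Among survivors only, the rejection rate is 0.044-0.059 in every setting, that is, nominal.

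**Hand check.** Let early deaths have a marker mean 1 SD higher, an OR of about e¹ = 2.7 per SD. Non-responders then exceed responders by the share s above, in SD units, and their variance is 1 + s(1 − s).

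- d = 5%: 273.6 responders, 206.4 non-responders, s = 0.116. SE = √(1/273.6 + 1.103/206.4) = 0.095, z = 1.23, rejection about 23%.
- d = 10%: 259.2 and 220.8, s = 0.217. SE = √(1/259.2 + 1.170/220.8) = 0.096, z = 2.27, rejection about 62%.

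Both agree with the OR 3 column, allowing for the slightly weaker association.

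**Does adjustment remove it?** Adding one covariate correlated 0.4 with the marker, at 10% deaths, changes 0.16 / 0.35 / 0.65 to 0.15 / 0.30 / 0.57. It helps a little.

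**The case against.** The strongest defence is that Research question 1 is a prediction question. Its objective is a classification system, and the stated benefit is less futile RT. For that purpose a patient who dies before benefiting is a failure, and a marker that identifies such patients is useful. The article gives this reason openly. This stands, and it is why the composite should remain the outcome for the response-score.

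The mechanistic question is mainly Research question 2, which models pain intensity over time without coding deaths as failures. This largely stands too: the Discussion ties therapeutic targets chiefly to change in pain intensity and calls the inflammation work, including RT response, explorative. It does not change the wording of Research question 1, under which a significant marker would be presented as a predictor of pain response.

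CRP is fitted beside Karnofsky status, metastases other than bone and comorbidity, so it is partly protected. The check above suggests that such adjustment reduces the inflation without removing it, and the cytokine and bone-marker step names no clinical covariates.

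The article speaks of CRP and advanced disease, not of death within weeks, nor of the other markers. It describes the population as advanced but not terminal. The marker-death link and the death rate are therefore assumptions.

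A sensitivity analysis may exist in an analysis plan that is not shown. The point here concerns how the article fixes and names the outcome.

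**Conclusion.** The point holds as a risk of misattribution. A marker related only to early death can reach significance for an outcome called pain response, and no step described in the article would reveal it. At 2% early deaths the inflation is slight (6-8% against a nominal 5%). At 5% it is 8-26% and at 10% it is 16-65%, depending on how strongly the marker predicts death. These figures rest on 480 evaluable patients, 60% response among survivors, a two-sided 5% test and the assumed ranges for the death rate and the association.

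A reader might infer that prognostic markers will be reported as predictors of RT analgesia, or that coding death as non-response is itself an error. The documents support neither. They give no early-death rate and no association between these markers and death within weeks, and the composite suits the aim of the score. The weakness is that the composite carries the name of one of its parts and is the only outcome behind the marker claims of Research question 1.

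**What to change.** 1. Keep the composite as the primary outcome for the response-score, and call it what it is: alive with pain response.
2. Report the number of deaths before week 3, and separately the number of living patients excluded as unassessed. Explain why the two groups are handled differently.
3. Pre-specify a supplementary analysis that repeats the CRP, biomarker and integrated models in patients alive and assessed at week 3.
4. Describe a marker as related to pain response, rather than to prognosis, only if its association is consistent in that analysis.
5. Use a three-category model (response, alive without response, died before week 3) only if the number of early deaths supports it, and then with few covariates. At 3-5% deaths there would be about 14-24 deaths among 480, against 29 clinical variables plus CRP plus centre. That is fewer than one death per coefficient (24 / 30 = 0.8), so the full model would be unstable.

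The cost is some wording, one more set of coefficients and slightly fewer patients, all on data already held. The supplementary analysis conditions on survival to week 3, a post-baseline event, so it belongs beside the composite and not in its place.
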